### Statistical analyses

The efficacy analyses will be conducted as both intention-to- treat (ITT; “as allocated”) and per protocol (PP; “as-treated”) since ITT can bias towards the null, leading to false claims of non-inferiority, and PP can fail to preserve the balance inherent to randomization (30, 31). For the analysis, the first step will be to examine demographic and clinical characteristics across study conditions to assess that the randomization worked as expected. If significant sociodemographic differences emerge, these variables will be included in the multivariate analyses since baseline adjustment has been shown to increase precision in randomized control trials (32). All analyses, for the factorial design, will be examined using a series of multilevel (or “mixed” effects) general linear regression models that account for clustering (via a random intercept) across sites. For these models, the independent variable of interest will be telemental health versus in-person START. The dependent variables will be calculated as change scores/differences since baseline. Two-way (Intervention group x time) interaction terms will test the primary study aim. Three-way (Intervention group x demographic population x time) interaction terms will test the secondary study aim. Effect sizes will be calculated using Cohen’s *d*. To accommodate increased false discovery rate, the study will adjust the significance threshold using the Benjamini-Hochberg procedure. This procedure is conducted after all tests are concluded; α = .01 will be assumed for the power analysis.

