**Methods:**

This study will take place within START (Systemic, Therapeutic, Assessment, Resources, and Treatment), a national evidence-based model of mental health crisis prevention and intervention for people with IDD. A total of 500 youth and adults, located across nine states, will be randomized 1:1 to telemental health vs. in-person. Participant inclusion criteria are ages 12–45 years, living in a family setting, and newly enrolled (within 90 days) to START. Outcomes will be assessed, using a non-inferiority design, for up to 1 year or until discharge. The intervention is comprised of four components: (1) outreach; (2) consultation/coping skills; (3) intake/assessment; and, (4) 24-hour crisis response. The in-person condition will deliver all components in-person. The telemental health condition will deliver components 1 & 2, via telephonic or other communication technology, and components 3 & 4 in-person. Outcomes include mental health crisis contacts, mental health symptoms, emergency psychiatric service use, perceived quality of mental healthcare, and time to discharge.

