### Intervention

START is a complex, multi-component intervention that includes four core elements: (1) outreach, service linkages, referrals, and training; (2) consultation and coping skill coaching; (3) intake and quarterly assessment; and, (4) 24-hour crisis response and intervention [21, 22]. As seen in Fig. 1, these components are based on START’s conceptual model, which is theory-driven and evidence-based. START teams consist of START Coordinators (master’s in social work or counseling) with caseloads of 20–30 people. The team also has a Clinical Director (PhD Clinical Psychologist), a Medical Director (Psychiatrist and/or Child Psychiatrist), and therapeutic coaches (BS/BA).

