### Comparators

This study compares in-person vs. telemental health START services. For in-person, this comparator will deliver all services and supports to persons with IDD and their families in-person, often in their homes. This is standard START practice. Due to the increased use of telecommunications in the field of healthcare, particularly since the COVID-19 pandemic, individuals in the in-person condition may have large healthcare planning meetings using telecommunication platforms such as Zoom^(TM)^. Use of telecommunications for healthcare planning, such as coordinating care and creating service linkages, will be tracked and assessed throughout the study. The telemental health condition will deliver components 1 & 2 via telephonic or other communication technology and components 3 & 4 in-person. Intake and quarterly assessment (component 3) and 24-hour urgent crisis response and intervention (component 4) will be provided in-person because this is needed to establish therapeutic rapport and ensure the safety of people with IDD and their families.

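### The per-protocol analysis is labelled as-treated, which gives up randomisation in the check on ITT; separately, the in-person comparator is described inconsistently

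*Protocol article*

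**What the plan says.** **Analysis sets.** The Statistical analyses section plans efficacy analyses by ITT, glossed as allocated, and by a second approach: "per protocol (PP; “as-treated”) since ITT can bias towards the null, leading to false claims of non-inferiority". The same sentence adds that "PP can fail to preserve the balance inherent to randomization". So the second analysis is there to check ITT, and the risk of lost balance is acknowledged.

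**What differs between the arms.** The Comparators section says: "The telemental health condition will deliver components 1 & 2 via telephonic or other communication technology and components 3 & 4 in-person". Only the delivery mode of components 1 and 2 is randomised.

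**The in-person arm.** The Abstract (Methods) says: "The in-person condition will deliver all components in-person". The Comparators section says "this comparator will deliver all services and supports to persons with IDD and their families in-person" and calls this standard START practice. It then says that "individuals in the in-person condition may have large healthcare planning meetings using telecommunication platforms", and continues: "Use of telecommunications for healthcare planning, such as coordinating care and creating service linkages, will be tracked and assessed throughout the study". The Intervention section lists component 1 as "1) outreach, service linkages, referrals, and training", so service linkages belong to one of the two randomised components.

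**The concern.** Per protocol and as-treated answer to different rules. Per protocol restricts the sample and leaves everyone in the arm to which they were randomised. As-treated moves people between arms, so the comparison becomes observational. The plan names one analysis and defines it as the other, in the very analysis it relies on because ITT may falsely favour non-inferiority. If telehealth participants who do badly had components 1 and 2 moved to in-person delivery, as-treated would carry their poor outcomes into the in-person arm and make telehealth look better.

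The comparator text raises a second, separate matter. If some linkage and planning work is remote in the in-person arm, the arms differ less than described. Because the use is permitted, a per-protocol set built on deviations would not remove it, so any loss of contrast would sit in both analyses.

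**Working it through.** The plan gives no figure for this point, so there is none to reproduce. The calculations below only show possible size.

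**Inputs from the article:** 500 participants randomised 1:1, so 250 per arm; FEIS margin 7 points, stated to equal 0.5 SD, so SD = 7/0.5 = 14; 99% interval, so z = 2.576 and one-sided error 0.005. **Assumptions:** no clustering; all switching rates, switcher prognoses, crisis risks and dilution shares.

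**1. As-treated, FEIS.** The true difference is −7, exactly at the margin. A share q = 0.10 of the telehealth arm (25 people) switches and is counted as in-person. Switchers' prognosis is b points worse than that of stayers, and they are taken to respond as in-person participants.

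- Bias = bq + 25·b(1−q)/275. For b = 7: 0.70 + 0.573 = +1.27.
- SE = 14·√(1/225 + 1/275) = 1.259.
- False-claim probability = Φ(bias/SE − 2.576).

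| Switchers' prognosis | Bias (points) | False-claim probability |
|---|---|---|
| 7 points worse | +1.27 | 0.059 |
| same | 0 | 0.005 |
| 7 points better | −1.27 | 0.0002 |

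**2. As-treated, crisis contact.** Assume true risks of 37% in-person and 51% telehealth. The 14-point gap is one reading of the 38% margin (0.37 × 0.38 = 0.1406). ITT gives +14.0 points, 99% upper limit 25.3. Let k = 25 telehealth participants be reclassified, a fraction f of whom had a crisis contact:

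- Telehealth risk = (127.5 − kf)/(250 − k); in-person risk = (92.5 + kf)/(250 + k).

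| f | Telehealth | In-person | Difference (points) | 99% upper limit |
|---|---|---|---|---|
| 1.00 | 45.6% | 42.7% | +2.8 | 14.3 |
| 0.75 | 48.3% | 40.5% | +7.9 | 19.4 |
| 0.51 | 51.0% | 38.3% | +12.7 | 24.2 |
| 0 | 56.7% | 33.6% | +23.0 | 34.3 |

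With 15% moved (k = 37.5) and f = 1, the difference is −2.9 points. That needs 37.5/127.5 = 29% of telehealth crisis cases to switch and nobody else.

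**3. The same 25 people under true per protocol.** Excluding them (f = 1) but keeping the randomised arms gives 102.5/225 = 45.6% against 37%: +8.6 points. The SE is √(0.456·0.544/225 + 0.37·0.63/250) = 0.0451, so the upper limit is 20.2. With a 14-point margin, Φ((0.14 − d)/SE − 2.576), where d is the observed difference, gives a false-claim probability of about 0.09 here. As-treated gives about 0.47 (d = 0.0283, SE = 0.0446). Per protocol is not unbiased either, but it is much less exposed.

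**4. Dilution, FEIS.** If a share c of the contrast is lost, the bias is 7c. With SE = 14·√(2/250) = 1.252, false-claim probability = Φ(7c/1.252 − 2.576):

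| c | 0 | 5% | 10% | 20% | 30% |
|---|---|---|---|---|---|
| 250 per arm | 0.005 | 0.011 | 0.022 | 0.072 | 0.184 |
| 128 per arm (the stated FEIS requirement) | 0.005 | 0.009 | 0.015 | 0.038 | 0.084 |

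The article does not say how much remote use to expect, so c is unknown.

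**The case against.** Four objections carry weight.

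- **Direction.** A reader might infer that both planned analyses are biased towards non-inferiority. The documents do not support that. As-treated bias depends on who switches, and the tables run both ways. The article itself warns of lost balance. In the crisis-contact example with 10% moved, even the extreme case leaves the expected upper limit at 14.3, just above a 14-point margin. This stands, and no direction is claimed here.
- **Mechanism.** Crisis response and quarterly assessment are in person in both arms by design. An in-person visit after a crisis is therefore assigned care, not a switch. Only a change in the delivery of components 1 and 2 would count, and the article describes no route or rate for that. This also stands.
- **Scope of the remote allowance.** A reader might infer that the in-person arm may receive component 1 remotely. The text covers large planning meetings, care coordination and service linkages. Nothing allows outreach visits, training, caregiver coaching or component 2 to be remote in that arm. The allowance is stated openly and its use is tracked. If it is part of in-person START as now practised, it narrows the question and does not bias the answer.
- **Deferred detail.** Deviation thresholds and a rule requiring both analyses to succeed are commonly left to the SAP, so their absence is not counted.

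None of this cures the label. The article does not leave the second analysis undefined: it equates it with a different one, and pairing it with the as-allocated gloss on ITT makes the literal reading plausible.

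**Conclusion.** The point holds in limited form.

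1. Per protocol is wrongly equated with as-treated. Taken literally, the check on ITT forfeits randomisation and is not dependable. The direction of bias is unknown; it would favour non-inferiority if telehealth participants who do badly have components 1 and 2 moved to in-person delivery. At 10% switching on FEIS, the false-claim probability ranges from 0.0002 to 0.059 around a nominal 0.005. The switching share and the 7-point prognosis gap are assumptions.
2. The statements that everything in the in-person arm is delivered in person do not agree with the remote planning and linkage work described in the Comparators section. This may dilute the contrast in both analyses. The amount is unstated, and the dilution table shows sensitivity, not an estimate.

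**What to change.** - In Statistical analyses, delete as-treated, or keep it only as a separately labelled supplementary analysis.
- Define the per-protocol set as analysed in the randomised arms, with deviation judged solely on the delivery mode of components 1 and 2. In-person crisis response and quarterly assessment then never count as departures.
- Reconcile the Abstract and the Comparators section by stating whether remote linkage and planning work is part of the in-person comparator or a departure from it. Use the telecommunication data already being tracked to apply that statement and to report the extent of remote use by arm.

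The cost is mainly wording, since the article already commits to tracking remote planning use. The downside is a somewhat smaller per-protocol set, more so if remote linkage work is declared a departure.

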### Perceived quality of mental healthcare

#### The family experiences interview schedule

The second outcome is family caregiver evaluation of their experiences with the mental healthcare system. This is assessed via the Family Experiences Interview Schedule (FEIS), a widely used semi-structured interview [24]. Baseline FEIS interviews are conducted by the START coordinator in the ordinary START intake process. Follow-up interviews will be conducted by an individual who was not involved with the person’s care. Interviews take approximately 20 min to complete. Three FEIS subscales will be used. The first (9 items) assesses family members’ appraisal of their own involvement as partners in treatment, the second Sect. (7 items) assesses perceived quality of services provided to the recipient, and the final Sect. (4 items) elicits feedback about how well the mental health system responds to the needs of family caregivers. Previous research across multiple samples has shown the FEIS and these subscales to be reliable (Cronbach’s α = 0.92) and internally valid [21].

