### Non-inferiority design

This study will employ a non-inferiority design. Non-inferiority trials permit a ‘new’ treatment to be considered efficacious if treatment effects fall within a pre-specified margin (the non-inferiority [NI] margin) of the effects identified in the reference treatment [27]. In this study, the ‘new treatment’ will be the telemental health condition, while the in-person condition will serve as the ‘established/reference treatment’. The merits of telemental health that justify consideration as an alternative to the standard of care include increased accessibility and lower cost. The merits of telemental health are assumed to be valuable enough that, even if effects fall slightly short of the reference treatment by a clinically tolerable amount, it is a viable alternative to the standard of care when circumstances would indicate its use [28].

The NI margin has been set for the FEIS, given its primacy in outcome. A 7-point change in the total FEIS score, which is equivalent to a standardized delta of 0.5, will identify the lower threshold for clinically meaningful difference [21]. Thus, a 99% confidence interval for the slope for the group assignment variable will be constructed and its lower limit will be compared to the − 7.0 non-inferiority margin. The 99% confidence interval, reflecting the α cutoff of 0.008, was selected to account for multiple comparisons, which will be determined post-hoc via the Benjamini Hotchberg procedure [29]. The non-inferiority margin for emergency service use will be a 38% reduction in the probability of a START crisis contact between START in-person and START telemental health. Last, we have identified a five-point change in the ABC irritability subscale as the non-inferiority margin. This study was registered on April 20th, 2022 on clinicaltrials.gov (NCT05336955; https://clinicaltrials.gov/ct2/show/NCT05336955 ).

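### Adjustment covariates are picked by significance tests of baseline imbalance, and no baseline outcome term is named beside the change scores, so the model is left to chance and the cited precision gain is not secured

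*Protocol article*

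**What the plan says.** All the main text is in the Statistical analyses section of the protocol article. The first analysis step is to "examine demographic and clinical characteristics across study conditions to assess that the randomization worked as expected". The rule that follows is: "If significant sociodemographic differences emerge, these variables will be included in the multivariate analyses". The reason given is "since baseline adjustment has been shown to increase precision in randomized control trials".

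On the form of the outcome: "The dependent variables will be calculated as change scores/differences since baseline". The models are "general linear regression models that account for clustering (via a random intercept) across sites". The terms named are study group, group by time, group by demographic population by time, the random site intercept, and any sociodemographic variable that passes the screen. There is no fixed covariate list. A baseline outcome term is neither named nor ruled out.

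The Non-inferiority design section shows where precision enters the decision. For the FEIS, "a 99% confidence interval for the slope for the group assignment variable will be constructed", and its lower limit is set against −7.0.

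**The concern.** Three things are wrong with the rule as written.

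- **It cannot do its stated job.** Allocation is random, at the individual level, and run by an independent party. A baseline difference is then a chance event, and a significant one does not show that randomisation failed.
- **It leaves the model open.** Which covariates enter is known only after the arms have been compared. In an unmasked non-inferiority trial the estimate set against the margin should come from a model fixed beforehand.
- **It does not follow from its own rationale.** The precision gain comes from prognostic covariates whether or not they are imbalanced. The screen selects on imbalance. It also admits only sociodemographic variables: clinical characteristics are compared, but have no stated route into the model.

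The most prognostic covariate is usually the baseline value of the outcome. The plan subtracts it, which fixes its slope at 1. Two features of this trial make a slope below 1 plausible. The Background says people enter START when in need, so regression to the mean is likely. For the FEIS, "Baseline FEIS interviews are conducted by the START coordinator in the ordinary START intake process", while follow-up is done by someone outside the person's care, which may weaken the baseline to follow-up correlation. At stake are an analysis model that is not fixed and intervals for the continuous outcomes that are wider than necessary.

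**Working it through.** **The plan's own figure.** Power analyses states 128 per group for FEIS change. With "A 7-point change in the total FEIS score, which is equivalent to a standardized delta of 0.5", 80% power and two-sided α 0.008, n = 2(2.652 + 0.842)²/0.5² ≈ 98 per group (85 if one-sided). So 128 does not reproduce. That is a separate matter, and nothing below depends on it; 128 serves only as the size of the simulated trial.

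**1. How often chance alters the model.** Inputs: k independent sociodemographic variables and a 0.05 screen. Both are assumptions, since the article defines neither. For scale, Study aims lists five subgroup factors. With correct randomisation, P(at least one enters) = 1 − 0.95^k:

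- k = 3: 14%
- k = 5: 23%
- k = 8: 34%
- k = 10: 40%

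**2. Whether the screen delivers precision.** Simulation: 128 per arm, change-score SD 14, margin −7, two-sided α 0.008, five modestly prognostic covariates, 4,000 runs for each ρ, no site clustering. Results for ρ = 0.3 / 0.5 / 0.7:

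| Analysis | Mean SE | Power |
|---|---|---|
| Change score, unadjusted | 1.75 / 1.75 / 1.75 | 0.90 / 0.91 / 0.90 |
| Change score with screened covariates | 1.75 / 1.75 / 1.75 | 0.91 / 0.92 / 0.91 |
| Baseline outcome as covariate | 1.41 / 1.52 / 1.62 | 0.99 / 0.97 / 0.95 |

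The screen changed the model in 22 to 23% of runs and left the mean standard error, which sets the interval width, where it was. The spread of the estimates themselves fell by only about 2 to 3% (for example 1.751 to 1.708 at ρ = 0.5). Type I error at the margin was 0.003 to 0.006 across all three analyses, against a nominal 0.004.

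**3. What the baseline term is worth for a continuous score.** Assume the same SD σ at baseline and follow-up, with correlation ρ.

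- Change-score variance: 2σ²(1 − ρ)
- Variance after baseline adjustment: σ²(1 − ρ²)
- Ratio: (1 + ρ)/2

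The table applies this to the FEIS at the planned 250 per arm. The SD of 14 (7/0.5) is read as the change-score SD, which is an assumption. The unadjusted SE is 14√(2/250) = 1.25, and the 99% half-width is 2.576 × SE.

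| Assumed ρ | Variance ratio | SE ratio | SE | 99% half-width | Equivalent extra participants, 2/(1+ρ) − 1 |
|---|---|---|---|---|---|
| Change score only | 1 | 1 | 1.25 | 3.23 | none |
| 0.3 | 0.65 | 0.81 | 1.01 | 2.60 | 54% |
| 0.5 | 0.75 | 0.87 | 1.08 | 2.79 | 33% |
| 0.7 | 0.85 | 0.92 | 1.15 | 2.97 | 18% |
| 0.9 | 0.95 | 0.97 | 1.22 | 3.14 | 5% |

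**4. Consequence for the FEIS decision at full size.** With true difference zero, power is Φ(7/1.25 − 2.652), above 0.99, even without the baseline term. With an assumed 30% loss (175 per arm), SE = 14√(2/175) = 1.50 and power is about 0.98.

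**The case against.** The case against is substantial in four places.

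- **The baseline term is unnamed, not excluded.** A reader might infer that the plan rules out baseline adjustment. The text does not say so. A change score with the baseline value as covariate gives the same treatment estimate as an analysis of the follow-up score, so the change-score sentence is compatible with the remedy, and an analysis plan not shown could supply the term. This stands. It does not touch the significance screen, which is stated outright.
- **The consequence for the decision is modest.** A reader might infer that the FEIS comparison is short of power because of this. On the article's own margin and planned size it is not (step 4). The simulated gains in step 2 are for about half the planned trial.
- **The formula has limits.** It needs equal SDs and a continuous score. It says nothing about the probability of a crisis contact, which sets the 250 per arm, or about time to discharge.
- **No bias is shown.** A reader might infer that screening distorts the estimate or inflates false claims of non-inferiority. The simulated type I error stayed near nominal. The change of FEIS interviewer is described without distinction by arm, so a constant shift cancels between arms; it can only lower ρ.

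Site is already handled by the random intercept, and the article does not show that emergency use before enrolment is recorded. What is left is a selection rule that is stated, is not supported by its own reason, and is easy to replace.

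**Conclusion.** The point holds in limited form. The covariate rule lets chance choose the model: about 23% of correctly randomised trials would be affected with five independent variables and a 0.05 screen, both assumed. It does not narrow the intervals, although precision is the reason given for it. For the continuous outcomes, naming the baseline score as a covariate would lower the variance of the treatment estimate to 0.65, 0.75 or 0.85 of the change-score value at an assumed ρ of 0.3, 0.5 or 0.7, given equal SDs. For the FEIS at 250 per arm and SD 14 this takes about 0.6 to 0.25 points off a 99% half-width of 3.23. The gain nearly vanishes as ρ approaches 1. No bias, type I error inflation or shortage of power is claimed. The change is recommended because it fixes the model in advance at almost no cost, not because the trial's conclusion is in danger.

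**What to change.** In Statistical analyses:

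1. Delete the conditional sentence and the statement that the baseline comparison tests randomisation. Report baseline characteristics by arm descriptively, without p-values.
2. Name a fixed set of prognostic covariates for all models, for example age and level of intellectual disability, and keep the random site intercept.
3. For each continuous outcome (FEIS, ABC subscales, START Plan stability), include its baseline value as a covariate. The dependent variable may be the follow-up or the change score.
4. For crisis and emergency-use models, include emergency use before enrolment if intake records it. Confirm this first.

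The cost is a small rewording of the model description, including how the group-by-time term is expressed. The baseline scores are already needed to form the change scores, so steps 1 to 3 should need little or no new data collection.

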### Assessments

Emergency service use and time-to-discharge will be assessed continuously throughout the 1-year study time line. All other assessments will be done at baseline, 6 (midpoint) and/or 12 (outcome) months, except for the START plan (which is conducted quarterly), the Family Experiences Interview, and the Person Experiences Interview (conducted at pre-post).

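### The primary aim is tested by a group-by-time interaction on change scores, which cannot be estimated for FEIS and PEIS and is blind to a constant deficit on ABC

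*Protocol article*

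**What the plan says.** Protocol article, Statistical analyses: "The dependent variables will be calculated as change scores/differences since baseline". The same paragraph then says "Two-way (Intervention group x time) interaction terms will test the primary study aim", and gives the secondary aim to a three-way interaction of group, demographic population and time. The models are "general linear regression models that account for clustering (via a random intercept) across sites".

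Assessments sets the schedule. The general rule is "All other assessments will be done at baseline, 6 (midpoint) and/or 12 (outcome) months"; among the exceptions are "the Family Experiences Interview, and the Person Experiences Interview (conducted at pre-post". FEIS and PEIS therefore have one baseline and one follow-up value. ABC falls under the general rule, so it has one or two follow-ups.

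Non-inferiority design describes a different test for FEIS: "a 99% confidence interval for the slope for the group assignment variable will be constructed", with its lower limit set against −7.0. The FEIS margin is "A 7-point change in the total FEIS score, which is equivalent to a standardized delta of 0.5". For ABC the section gives "a five-point change in the ABC irritability subscale as the non-inferiority margin" but names no coefficient or interval to compare with it. Power analyses sizes FEIS on the difference between arms in change from baseline to follow-up.

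**The concern.** Group by time is the right term when the outcome is the raw score and baseline is one of the time points: it then measures how much more one arm changed than the other. Subtracting baseline already does that job. With a change score as the outcome, the arm difference sits in the group term, and group by time measures only how that difference shifts from one follow-up visit to the next.

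In a non-inferiority trial this matters in a particular direction. A telemental health deficit that is present at 6 months and still present at 12 months is the result the trial has to be able to detect, and it leaves the interaction at zero. For the outcomes with a single follow-up, the stated test cannot be computed, and the analyst would have to choose another coefficient after the data are in.

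**Working it through.** **The plan's own figure.** Power analyses gives 128 per group for FEIS, for a between-arm difference in change. With a standardized difference of 0.5 (7 points, implied SD 7/0.5 = 14), 80% power and two-sided α = 0.008:

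n = 2 × (2.652 + 0.842)² / 0.5² = 98 per group (85 if α is one-sided).

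The stated 128 is not reproduced. That is a separate matter; what counts here is that the quantity sized is the group difference, not an interaction.

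**FEIS and PEIS.** The model columns are intercept, group, time, and group × time. With one change score per person, time takes a single value, so the time column is a multiple of the intercept and group × time is a multiple of group. The four columns have rank 2, and the interaction cannot be separated from group.

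**ABC with both follow-ups.** Score the outcome as improvement, so that a negative arm difference favours in-person. With time coded 0 at 6 months and 1 at 12 months, the four columns have rank 4, and

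group = d6; group × time = d12 − d6.

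| Constant deficit | group | group × time |
|---|---|---|
| 5 | −5 | 0 |
| 8 | −8 | 0 |
| 10 | −10 | 0 |

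If only one follow-up is taken, ABC is in the same position as FEIS.

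**How often this would mislead for ABC.** The article does not say how the interaction would be judged. Suppose its 99% interval were compared with −5. Assumptions: 250 per arm (500 randomized 1:1); SD of change 10 (the stated 100 per condition implies 5 / [(2.652 + 0.842) × √(2/100)] = 10.1); correlation ρ between the two change scores of 0.3 to 0.7. At ρ = 0.5:

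- True SE of the interaction = 10 × √(2 × 0.5 × 2/250) = 0.894. With this SE, P(non-inferior declared) = Φ(5/0.894 − 2.576) = 0.999.
- SE if a person's two rows are treated as independent = 10 × √(4/250) = 1.265. Then P = Φ[(5 − 2.576 × 1.265)/0.894] = 0.974.

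Over ρ = 0.3 to 0.7 these become 0.984 to 1.000 and 0.950 to 0.994. With SD 8 to 12 the ranges are 0.91 to 1.00 and 0.81 to 1.00. With 100 per arm and SD 10 they are 0.66 to 0.98 and 0.45 to 0.46. These probabilities are the same for any constant deficit, since the interaction is zero in every case. A valid test on the group difference would wrongly declare non-inferiority 0.5% of the time when the true deficit equals the margin.

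**Secondary aim.** By the same algebra, the three-way term is inseparable from group × subgroup when there is one change score per person, and is zero when a subgroup's deficit is the same at both visits.

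**Within-person correlation.** Suppose no participant term is fitted and two change scores per person are used.

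- Arm difference at one visit: true variance 2 SD²/n, and the independent-rows model uses the same 2 SD²/n. There is no inflation.
- Arm difference averaged over both visits: true variance SD²(1 + ρ)/n against SD²/n assumed. One-sided error = 1 − Φ(2.576/√(1 + ρ)), which is 0.012, 0.018 and 0.024 for ρ = 0.3, 0.5 and 0.7, against a nominal 0.005.
- Interaction: its variance is overstated by 1/(1 − ρ), so that test is too wide, not too narrow.

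**The case against.** The strongest reply is that the rest of the article points the right way. Statistical analyses names the arm comparison as the independent variable of interest, Non-inferiority design fixes the FEIS decision on the group coefficient, and Power analyses sizes the arm difference. On this view one sentence has slipped. That holds for FEIS: a reader might infer that the trial has no usable FEIS test, and the documents do not support that, because the rule in Non-inferiority design can be computed and would catch a persistent deficit. It does not rescue ABC, where a margin stands without a coefficient and the interaction sentence is the only stated test. Nor is the group coefficient fixed once group × time is in the model, since it is then the difference at whichever time is coded zero.

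A second reply is that the authors may have meant raw scores, or baseline rows entered as zero change, in which case group × time would equal the difference in change. The text says change scores, does not describe such rows, and rows fixed at zero have no variance.

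A reader might also infer that the model treats repeated rows from one person as independent and so makes every group interval too narrow. The documents do not support this. A site intercept is the only random effect named, but a condensed article may leave the participant-level structure to the full plan. Even without that structure, FEIS and any single-visit contrast are unaffected; only an effect averaged over visits would be, and the article specifies no such average.

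Finally, an unadjusted comparison of change scores is valid in a randomized trial. Adjusting for the baseline score gains precision and is a preference, not the correction of an error.

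**Conclusion.** The point holds. As written, the stated test of the primary aim is not computable for FEIS and PEIS. For ABC it is zero under any constant deficit if both follow-ups are used, and not computable if only one is. It conflicts with Non-inferiority design and Power analyses, and the secondary-aim interaction has the same fault. These conclusions follow from the text and simple algebra and need no assumed values.

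The probability of wrongly declaring ABC non-inferior at the margin (about 95 to 99% at 250 per arm with rows treated as independent, higher with the correct SE, against 0.5%) does rest on assumptions: two follow-ups, SD 10, ρ 0.3 to 0.7, and the interaction interval being compared with −5. The participant-level term is a secondary matter. No claim is made here about crisis contacts or time to discharge. The sentence must be corrected before analysis, because otherwise the coefficient that decides non-inferiority is left open.

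**What to change.** - Delete the sentence that gives the primary aim to the group-by-time interaction.
- For FEIS and ABC, define the non-inferiority contrast as the between-arm difference at a named follow-up time (for example 12 months), preferably adjusted for the baseline score. Compare its confidence interval with the margin, stating the sign for each scale. Use the same contrast in Non-inferiority design, Statistical analyses and Power analyses.
- State whether ABC is collected at 6 months, 12 months or both.
- Test the secondary aim with group × subgroup at that same time point.
- Where several follow-up visits are modelled together, include a participant-level random effect or a within-person covariance structure.

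The cost is wording in the protocol and analysis plan. Settling the ABC schedule clarifies what is already planned; no further participants are needed.
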